#### Cohort study among partners of cancer survivors

The primary outcomes for partners are working hours per week and health-related quality of life. Secondary outcomes include change in working hours (as a percentage of the contract hours at baseline), ‘employment status’ (at work/not at work), sick leave, health-related work functioning, caregiver burden and depression. Information on a number of additional parameters (see Table 1 for a full overview) will be gathered to describe the study sample and/or as predictors in the prediction model.

### Statistical analyses

For hardcopy questionnaires, data entry will be verified by a 10% double data entry check. In preliminary analyses, for both the RCT and cohort study, item frequencies and missing data will be examined. Patterns of missing data will be assessed to determine non-ignorable dropout. Scores for the included scales will be calculated according to established scoring algorithms (as described in more details in Table 2). All analyses will be performed using SPSS 22.0 [45], and a two-tailed significance level of 0.05 will be considered statistically significant.

#### RCT among cancer survivors

Representativeness of participants will be evaluated by comparing cancer survivors who are included in the RCT with aggregated data of all potentially eligible cancer survivors from the NCR, using students’ t-test or appropriate non-parametric tests for the following characteristics: gender, age, time of diagnosis, tumour type and stadium and treatment. Moreover, reason of non-response at baseline (from the answer card) and during the follow-up period will be tabulated to get a better understanding of the representativeness of the study sample.

Baseline sociodemographic and clinical characteristics of the intervention group and the control group will be described and compared. Primarily, all analyses will be conducted on an intention-to-treat basis. In addition, per-protocol analyses will be carried out, in which only cancer survivors who fully complete the intervention according to protocol (i.e., having completed a minimum of three sessions: an introductory session, at least one one-on-one session with an occupational therapist, and at least one session with the reintegration consultant) will be compared to the control group.

To evaluate between-group differences on the aforementioned primary and secondary outcomes, generalized estimating equations (GEE) for longitudinal data (i.e., with the primary and secondary outcomes at six (T1) and 12 months of follow-up (T2)) will be used, adjusted for baseline values of the outcome and using appropriate tests for ordered and continuous data. This approach accounts for correlated within-subject responses, allows for non-normally distributed variables and deals adequately with missing data [46–48]. If the data are not missing completely at random, non-ignorable drop-out will be adjusted for [49]. Short- (T1) and long-term (T2) effects of the intervention will be reported separately. Effect sizes will be expressed in beta, with 95% confidence interval.

The secondary outcome ‘time to RTW’ will be analysed with time-to-event analysis [50]. A Kaplan-Meier curve will be drawn, and differences between the two groups will be tested with the log rank test. In addition, the Cox proportional hazard model of survival analysis will be applied to estimate hazard ratios and the corresponding 95% confidence intervals.

For all analyses, unadjusted models and models adjusted for relevant confounders will be presented. In addition to the main analysis described above, subgroup analyses will be performed (see Table 1 for a list of potential confounders and subgroups). No interim analyses will be conducted for this study, as due to the low risk of the intervention it is unlikely that results of such analyses would lead to termination of the study.

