### Sample size calculation

#### RCT among cancer survivors

The RCT sample size calculation is based on the primary self-reported outcome measure, i.e., working hours per week. Based on previous research [23], a standard deviation of 13 h per week was assumed, and a between group (intervention versus control) effect of 5.5 h per week is expected. Given this effect size, with a power of 80% and level of statistical significance set at *p*-value< 0.05, the sample size required is 88 cancer survivors in each group (176 in total). In this study 236 cancer survivors will be recruited, to allow for an attrition rate of approximately 25% (i.e., cancer survivors who discontinue participation in the study entirely, including failure to complete the follow-up questionnaires) and to enable subgroup analyses.

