### Process evaluation RCT

Alongside the RCT, a process evaluation will be conducted using the RE-AIM (Reach, Effectiveness, Adoption, Implementation, and Maintenance) framework [53], to examine the STEPS intervention regarding feasibility, experiences, satisfaction, barriers and facilitators for implementation. The RE-AIM framework has been adjusted to the design and target population of this study (see Table 3 for an overview), e.g., adding the dimension ‘tailoring’ to the framework. The measurements of the process evaluation will be based on data collected during the study and data collected by process evaluation questionnaires. To do so, cancer survivors in the intervention group will receive a short questionnaire, together with the six-month follow-up questionnaire (T1). Cancer survivors in the control group will be asked what care they have received during the study period. Participating occupational therapists and reintegration consultants will receive their own specified questionnaire at the end of the intervention period.

**Table 3 Tab3:** Overview of process measures according to the Re-Aim framework

Dimensions	Topics	Assessment method
Reach (individual level)	1. Patient response versus nonresponse rate. 2. Characteristics of participants compared to non-participants. 3. Percentage of patients who completed the intervention.	1. Response and non-response data. 2. Percentages excluded and reasons for exclusion (using drop-out and loss-to-follow-up data, reported reasons for declining participation, data from NCR on source population). 3. Process evaluation questionnaire (patient version).
Effectiveness (individual level)	4. Effect of the intervention on primary and secondary outcomes. 5. Unintended adverse effects of the program.	4. Data regarding primary and secondary outcome measures. 5. Self-reported in process evaluation questionnaire.
Tailoring (individual level)	6. Extent to which the content, intensity, and duration of the intervention was tailored to the patient’s needs, limitations, wishes and capacities. 7. Extent to which the intervention enabled the patient to return to work or continue work. 8. Extent to which the return-to-work/work retention plan fitted the work-related needs, capacities and wishes of the patient.	6–8. Process evaluation questionnaire (patient version).

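### Representativeness is tested against an NCR pool that contains the participants, with no estimate or interval named, so a non-significant result would not show that the sample is representative

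*Protocol article*

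**What the plan says.** Under Statistical analyses, RCT among cancer survivors, the comparison is set out as follows: "Representativeness of participants will be evaluated by comparing cancer survivors who are included in the RCT with aggregated data of all potentially eligible cancer survivors". The aggregated data come from the NCR, and the comparison is carried out "using students’ t-test or appropriate non-parametric tests for the following characteristics: gender, age, time of diagnosis, tumour type and stadium and treatment". The opening paragraph of Statistical analyses covers all analyses: "a two-tailed significance level of 0.05 will be considered statistically significant". For the trial outcomes the same section asks for a beta with a 95% confidence interval. For representativeness it names only tests.

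Three other places bear on the point.
- Study procedures, RCT among cancer survivors: the NCR is the main way of identifying candidates. Social media, patient organisations and walk-in centres are additional routes.
- The sentence after the representativeness tests: reasons for non-response will be tabulated.
- Process evaluation RCT, Table 3 (Reach): the item "Characteristics of participants compared to non-participants", drawing among other sources on NCR data about the source population. No statistic is named there.

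**The concern.** Asking whether a sample is representative is asking whether it is similar to the population behind it. A difference test that fails to reject does not answer that, because it may reflect a small difference or too little information. Without an estimate and an interval the reader cannot tell which.

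The choice of comparator adds to this. All potentially eligible survivors in the NCR include those who went on to join the trial through the NCR. Setting a subgroup against a whole that contains it shrinks the observed difference. The ordinary two-sample standard error also treats the groups as independent and comes out too large. Both effects push towards no difference.

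What is at stake is what can be said about whom the STEPS result applies to. The protocol itself expects selection: under Methodological considerations it foresees that some survivors may be underrepresented because recruitment starts soon after diagnosis.

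**Working it through.** **The plan's own figure.** No number is stated for the representativeness comparison. The sample size that supplies the 236 does reproduce. With an SD of 13 h and a difference of 5.5 h, 2 × (1.960 + 0.842)² × (13/5.5)² = 87.7, so 88 per group and 176 in total. Then 176/0.75 = 234.7, against 236 stated.

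**Inputs.** From the documents: m = 236 participants (Sample size calculation) and alpha 0.05 two-sided. Assumed, because the documents do not give them:
- pool size N of 1,000, 2,000 or 10,000, participants included;
- all 236 participants inside the pool;
- a true difference d of 0.1 to 0.3 SD between participants and non-participants;
- a normal approximation with a common SD.

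**Formulas, in SD units.**
- Expected difference, participants minus whole pool: D = d × (1 − m/N).
- Standard error used by an ordinary two-sample test: S = √(1/m + 1/N).
- True standard error given the overlap: T = (1 − m/N) × √(1/m + 1/(N − m)) = √(1/m − 1/N).
- True size: 2 × [1 − Φ(1.96 S/T)].
- Chance of missing the difference: Φ((1.96 S − D)/T) − Φ((−1.96 S − D)/T).

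**Worked case, N = 1,000.** S = √(1/236 + 1/1,000) = 0.0724 and T = √(1/236 − 1/1,000) = 0.0569, so S is 1.27 times too large. The size is 2 × [1 − Φ(2.493)] = 1.3%. For d = 0.2, D = 0.2 × 0.764 = 0.153 and the critical difference is 1.96 × 0.0724 = 0.142. Then (0.142 − 0.153)/0.0569 = −0.19, and Φ(−0.19) = 42% missed (the second term is negligible).

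**Results.** In brackets: the miss rate when the comparator is the N − 236 non-participants.

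| N | S | T | S/T | True size | Missed, d = 0.1 | Missed, d = 0.2 | Missed, d = 0.3 |
|---|---|---|---|---|---|---|---|
| 1,000 | 0.0724 | 0.0569 | 1.27 | 1.3% | 87% (73%) | 42% (23%) | 6% (2%) |
| 2,000 | 0.0688 | 0.0611 | 1.13 | 2.7% | 78% (70%) | 25% (18%) | 2% (1%) |
| 10,000 | 0.0659 | 0.0643 | 1.02 | 4.5% | 69% (67%) | 15% (14%) | under 1% (under 1%) |

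A characteristic at 50% in non-participants and 60% in participants behaves like d = 0.2: 42%, 24% and 15% missed.

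**Precision with the non-overlapping comparator.** The 95% CI half-width is 1.96 × √(1/236 + 1/(N − 236)) = 0.146, 0.136 and 0.129 SD for the three pool sizes, or about 7.3, 6.8 and 6.5 percentage points for a proportion near 50%.

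The brackets separate the two problems. Removing the overlap helps most in a small pool. Even without overlap, a 0.1 SD difference is missed about 67% to 73% of the time, so an interval is still needed.

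**The case against.** Several stronger readings are tempting, and the documents do not support them.

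- **That the plan treats a non-significant result as proof of representativeness.** No sentence says so. The article states a comparison, a family of tests and an alpha, but no decision rule. The risk lies in how the result might be read.
- **That tests are the sole evidence.** Reasons for non-response are also tabulated, and Table 3 plans a comparison with non-participants, which does not overlap. These soften the point but do not remove it: reasons do not measure selection on the listed characteristics, and Table 3 names no statistic.
- **That the two comparators contradict each other.** Both comparisons can be made. Table 3 simply has the better one.
- **That the tests do not suit categorical characteristics or aggregated data.** The wording allows appropriate non-parametric tests, which can include chi-square, and frequency tables suffice for that and for ranks on ordered categories.

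On size, the pool and the degree of overlap are unknown, and recruits from social media or patient organisations need not be in the pool. Once the pool reaches several thousand the overlap matters little, and 0.3 SD is missed at most about 6% of the time at the sizes assumed. That all stands. One could add that a condensed article may leave estimates and intervals to the fuller plan. But the article does fix the comparator and the tests, and those are what should change.

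**Conclusion.** The point holds as a cheap improvement to a descriptive check. The stated comparator contains the NCR-route participants, so the test is diluted and conservative. With no estimate or interval named, a non-significant result would not show that the sample is representative.

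Under full overlap the effect is clear in a pool of 1,000 and minor in a pool of 10,000. With partial overlap it lies between the overlapping and the bracketed figures in the table. Pool size, overlap share and what counts as a material difference are all assumptions. Randomisation, the primary effect estimate and the sample size are not touched; only statements about whom the result applies to are.

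**What to change.** In the representativeness paragraph of the RCT analysis section:
1. Compare NCR-route participants with eligible non-participants, consistent with Table 3. The comparator comes from the NCR aggregate by subtraction: for counts, pool minus participants; for means, (N × pool mean − m × participant mean)/(N − m), where m here counts the NCR-route participants only.
2. Report a standardised difference, or a difference in proportions by category, with a 95% CI for each characteristic, in place of relying on p-values.
3. Show recruits from social media and patient organisations separately.
4. State that a non-significant difference will not be interpreted as representativeness.

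A pre-stated bound, for example 0.2 SD, is optional.

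The cost is a few lines of text and one descriptive table, with no extra patients or data collection. Participants' characteristics must be coded as in the registry for the subtraction to work. The downside is precision: with half-widths of about 0.13 to 0.15 SD, some characteristics will have to be reported as inconclusive.

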### Participants and recruitment

#### RCT among cancer survivors

Cancer survivors of working age (18–63 years at time of diagnosis), with histologically confirmed cancer and a life expectancy of more than 1 year will be recruited. At study entry, eligible cancer survivors have a fixed or temporary employment contract, with at least 6 months left of their contract, and a history of paid work for at least 1 year prior to diagnosis (with ≥8 contracted working hours per week). Cancer survivors can both be at work or (partly) on sick leave when entering the study. Cancer survivors will be recruited 3–18 months post-diagnosis. The cut-off for the maximum time post-diagnosis was set at 18 months for cancer survivors to be able to complete the intervention (with a maximum duration of 6 months) before a potential work disability assessment. According to Dutch legislation, work disability assessments take place after two years of sick leave to determine whether someone is disabled for work or not and may receive work disability benefits or not. Regardless of the outcome of the work disability assessment, employers are allowed to terminate the employment contract after 2 years of sick leave. Moreover, cancer survivors will be eligible for participation in STEPS if they are, or have been, treated with at least radiotherapy and/or chemotherapy. Previous research has shown that cancer survivors who received complex treatments, i.e., chemotherapy, radiotherapy, or a combination thereof, indicated lower work ability than cancer survivors who were treated with surgery alone [22]. Cancer survivors with additional treatment modalities, besides radiotherapy and/or chemotherapy, will be eligible for participation as well.

Cancer survivors will be excluded if their treating physicians consider work unfeasible, if cancer survivors have serious cognitive or psychiatric problems, or other comorbidities that would preclude them from participating in the intervention program, and/or if cancer survivors lack basic proficiency in Dutch. Cancer survivors participating in concurrent studies or rehabilitation programs aimed at sustained employment, or cancer survivors who refuse the involvement of their employer in the STEPS intervention will also be excluded.

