### Study procedures

#### RCT among cancer survivors

The main route of identification of potentially eligible cancer survivors is through the Netherlands Cancer Registry (NCR). Data managers of the NCR will develop a query based on (a selection of) aforementioned inclusion/exclusion criteria supplied by the researchers. The query will be performed once retrospectively (3–18 months), and prospectively every 3 months for 1 year. The list of potentially eligible cancer survivors will be sent to the involved medical specialist of a participating hospital, who will check whether these cancer survivors are indeed potentially eligible for participation. All potentially eligible cancer survivors will receive an information package with an invitation letter on behalf of the involved medical specialist of the participating hospital, an information brochure, a screening informed consent form, a screening questionnaire and a non-response answer card. If interested, cancer survivors will be asked to sign the screening informed consent form, complete the screening questionnaire and send these documents to the researchers. Cancer survivors will be asked to take a legally mandatory reflection period of at least 1 week before agreeing to participate. Survivors who are not interested in participating can complete a short non-response answer card on which they can indicate their reasons of non-response.

Cancer survivors who meet the inclusion criteria based on the screening questionnaire, will receive a telephone call from a research assistant during which they will be further informed about the project, in- and exclusion criteria will be confirmed, and they will have the opportunity to ask questions. If the cancer survivors’ eligibility is confirmed, they will be asked to sign a second informed consent form for study participation, and subsequently to complete the baseline questionnaire. Upon return of the completed baseline questionnaire, randomisation will take place.

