Next to identification via the NCR and recruitment through hospitals, cancer survivors will be recruited through social media channels and (e-mail) messages of the Dutch Federation for Cancer Patient Organizations (NFK), Kanker.nl (a Dutch platform for cancer survivors), and psychosocial oncology walk-in centres (Instellingen PsychoSociale Oncologie; IPSO). Cancer survivors can contact the research team if they wish to receive aforementioned information package. This package will then be sent via post, after which the recruitment procedure is identical to that described above.

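### The planned comparison of RCT participants with the NCR pool mixes eligibility rules and recruitment route with selective participation, so by itself it cannot show whether participants represent eligible employed survivors

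*Protocol article*

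**What the plan says.** Under Statistical analyses (RCT among cancer survivors), the protocol article evaluates representativeness by "comparing cancer survivors who are included in the RCT with aggregated data of all potentially eligible cancer survivors from the NCR". The tests are t-tests or non-parametric tests on gender, age, time of diagnosis, tumour type and stage, and treatment. The general analysis text sets a two-sided 0.05 level. Reasons for non-response are tabulated alongside.

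Study procedures describes how the NCR pool arises: "Data managers of the NCR will develop a query based on (a selection of) aforementioned inclusion/exclusion criteria supplied by the researchers". The list then goes to the treating specialist, "who will check whether these cancer survivors are indeed potentially eligible for participation". Full eligibility is settled only for those who return the screening questionnaire and are then telephoned, when "in- and exclusion criteria will be confirmed, and they will have the opportunity to ask questions".

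Participants and recruitment sets criteria that reach well beyond cancer diagnosis and treatment. For example, "eligible cancer survivors have a fixed or temporary employment contract, with at least 6 months left of their contract", and "cancer survivors who refuse the involvement of their employer in the STEPS intervention will also be excluded". At least a year of paid work before diagnosis and basic Dutch are also required.

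Study procedures adds a second way in: "cancer survivors will be recruited through social media channels and (e-mail) messages of the Dutch Federation for Cancer Patient Organizations (NFK", and likewise through Kanker.nl and the IPSO walk-in centres.

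**The concern.** The two sides of the comparison are different populations. Everyone on the RCT side has met all the criteria. The NCR side has been filtered on some of them, and appears to include people who could never enrol, such as those without an employment contract and the self-employed. The RCT side may also hold people who did not come through the NCR list.

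A difference in, say, age can therefore arise in three ways: the eligibility rules select by age, the open routes attract a different age group, or eligible people of different ages accept at different rates. No work variable is among the characteristics compared, so the comparison cannot separate these. Opposing effects can also cancel, so a non-significant result gives no assurance either.

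At stake is the statement about whom the result applies to, together with the Reach part of the process evaluation (Table 3). Methodological considerations foresees recruitment difficulty and possible underrepresentation, and suggests that the programme's inclusiveness might reduce selection by age, tumour type and gender. All three are variables in this comparison.

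**Working it through.** **1. The plan's own figures.** The only figure used here is the RCT size. With SD 13, difference 5.5, two-sided 0.05 and 80% power, the sample size is 88 per arm (power 0.801), 176 in total. Allowing for 25% attrition, 176/0.75 gives 235, against 236 stated. This reproduces, and nothing below alters it.

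**2. The two sides.**

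| | NCR side | RCT side |
|---|---|---|
| Criteria applied | a selection, by query; perhaps also the specialist check | all |
| Contract, work history, Dutch, employer involvement | apparently not applied | applied |
| Route | NCR | NCR, plus social media and patient organisations |

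The article does not list the criteria that the query omits. That the employment criteria are among them is inferred from their confirmation at the later screening steps. Refusal of employer involvement depends on the person's own answer, so a registry query is unlikely to apply it.

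**3. How large could the eligibility effect be?** The documents give no pool size, eligible share or age distribution. The following are assumptions: pool M = 5,000; age SD 9 years; a share π of the pool truly eligible; ineligible members differing from eligible ones by D years in mean age. The n = 236 participants are taken to be a perfectly random sample of the eligible.

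- Expected difference, participants against pool: (1 − π) × D in absolute value.
- Standard error: 9 × √(1/236 + 1/5000) = 0.60 years.
- Probability of p < 0.05: Φ(shift/SE − 1.96) + Φ(−shift/SE − 1.96).

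| π | D = 2 | D = 4 | D = 6 |
|---|---|---|---|
| 0.8 | shift 0.4: 0.10 | 0.8: 0.27 | 1.2: 0.52 |
| 0.6 | 0.8: 0.27 | 1.6: 0.76 | 2.4: 0.98 |
| 0.4 | 1.2: 0.52 | 2.4: 0.98 | 3.6: >0.99 |

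With D = 0 the value is 0.05, so the excess comes entirely from the mismatch.

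**4. Masking.** Take π = 0.6 and D = 4. If selective participation moves the participants' mean age by 1.6 years towards the ineligible group, the expected difference from the pool is zero and the planned test rejects at about 5%. A comparison with the eligible part of the pool (0.6 × 5,000 = 3,000) would reject with probability 0.75.

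**5. Route.** Suppose, again by assumption, a pool of 3,000 with 55% women, and 20% of participants from open recruitment, of whom 75% to 85% are women. The share of women among participants is then 0.8 × 0.55 + 0.2 × 0.75 = 0.59, rising to 0.61 at 85%. A two-sample test of proportions is significant with probability 0.22 to 0.43, with no selection at all among those who came through the NCR.

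**The case against.** There is a fair case that this is mainly a matter of labelling, and several parts of it stand.

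- The article states no rule by which the sample would be called unrepresentative, and openly calls the comparator potentially eligible and aggregated. A reader might infer that a faithful sample will be declared unrepresentative, or that a stated 5% error rate is breached. The documents do not support that, because they attach no such hypothesis or verdict to the tests.
- Comparing a trial sample with its source population is itself a legitimate check of external validity. That is right, provided the result is described as such.
- Table 3 already plans response rates, participant against non-participant characteristics, percentages excluded with reasons, and recruitment path (item 11). These help, but the NCR comparison does not use the recruitment path, and the Reach entry draws on the same NCR source population.
- A reader might infer that open-route recruits come from another population. That goes too far: Design and setting confines the trial to survivors treated in participating hospitals, so such recruits may also appear in the NCR. Route can still change the mix of participants.
- The pool may be taken after the specialist check, which would narrow it. It would still be only potentially eligible.
- Every magnitude above is assumed. The figures show what is possible, not what is likely.

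What remains is the mismatch itself, which neither the tabulated non-response reasons nor Table 3 removes. The article fixes the comparator, the variables and the tests, so this is not simply a detail left to a fuller document.

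**Conclusion.** The point holds in a limited form. As planned, the NCR comparison combines the effects of the eligibility rules and the recruitment route with selective participation. Neither a significant nor a non-significant result can by itself show whether participants represent eligible employed survivors. The size of the distortion cannot be determined from the documents. Under the assumptions shown it ranges from slight (0.10 against 0.05) to near certainty of a significant result. The conclusion rests on two readings: that the employment-related criteria are among those the query omits, and that the RCT side includes every recruitment route. The article strongly suggests the first without listing the criteria; the second follows from its wording. Randomisation, the primary estimate, power and sample size are unaffected. This is an inexpensive improvement to an external-validity analysis, not a threat to the trial's main result.

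**What to change.** Under Statistical analyses (RCT among cancer survivors):

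1. Use the recruitment-path information already planned in Table 3, item 11, to report the NCR comparison for NCR-route participants as well as for all participants.
2. Replace the 0.05 tests with standardised differences and 95% confidence intervals.
3. Label the comparator as survivors on the NCR list (source population), and state whether it is taken before or after the specialist check. Draw no conclusion about eligible employed survivors from this comparison alone. Present it beside the exclusion and non-response figures planned in Table 3.

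A comparison with known-eligible non-participants should not become the main basis for the representativeness statement. The NCR data are aggregated, the non-response card is described as giving reasons only, and those who screen as eligible and then decline leave out the silent non-responders.

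The cost is wording and one extra column of results, with no added patients, visits or questionnaires. The NCR-route comparison is less precise. With an assumed pool of 5,000, the half-width of the interval for a standardised difference is 1.96 × √(1/236 + 1/5000) = 0.13 for all participants. It becomes 1.96 × √(1/150 + 1/5000) = 0.16 if, by assumption, 150 came through the NCR. The statement on representativeness also becomes more modest.
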